##### Participation of the healthy controls

2.3.1.2

Participants who will meet the following criteria will be included:1.Age of 19 to 35 years.2.BMI of 18.5 to 23 kg/m^2^.3.No evidence of acne.4.(Only for women) regular menstrual cycle during the last 3 months.5.No digestive-related uncomfortable symptoms in usual situations.6.No abdominal muscle tension.7.Other disorders that may affect the outcomes.8.Voluntary participation in this clinical trial.

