##### Participation of the population with acne vulgaris

2.3.1.1

Participants who will meet the following criteria will be included:1.Age of 19 to 35 years.2.Body mass index (BMI) of 18.5 to 23 kg/m^2^.3.Acne vulgaris [20 individuals with Korean Acne Grading System (KAGS) Gr 1 or 2; 20 individuals with KAGS Gr 3 or 4; and 20 individuals with over KAGS Gr 5).4.Voluntary participation in this clinical trial.

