##### Exclusion criteria

2.3.1.3

Participants who will meet any of the following will be excluded:1.Use of oral steroids, oral contraceptives, oral vitamin A derivatives, antibiotics, or herbal medicines that may affect the test results during the last 4 weeks.2.No fasting for more than 8 hours after 9:00 pm on the day before the visit.3.Alcohol drinking within the last week.4.Smoking.5.Pregnancy or lactation.6.Judgment that physical or mental testing is not appropriate for the clinical trial.7.Participation in other clinical trials that may affect this trial.

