#### Questionnaire

2.5.1

The participants will complete a questionnaire that would include general sociodemographic information (e.g., age and sex), personal habits (e.g., smoking, alcohol consumption, sleep pattern, and dietary habits),^[4,13]^ anthropometric measurements (e.g., height, weight, and BMI), pregnancy, menstrual pattern and history, use of oral contraceptives, history of adolescence acne, history of acne in relatives, relevant comorbidities (e.g., polycystic ovary syndrome, hirsutism, type II diabetes, and thyroid disease), acne pattern identification,^[14]^ and stress level during the last month, which will be self-assessed in accordance with the stress response inventory.^[15]^

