#### Exploring biomarker with metabolomic profiling

2.5.4

This study will apply MS-based metabolomic profiling studies for the detection and identification of potential metabolic biomarkers for acne in the participants’ serum. The liquid chromatography-mass spectrometry system will consist of a Thermo Scientific Vanquish ultra-high-performance liquid chromatography (UHPLC) system (Thermo Fisher Scientific, Sunnyvale, CA) with a triple ToF 5600+ mass spectrometer system (Triple ToF MS) (SCIEX, Foster City, CA) for untargeted metabolite analysis. The UHPLC system with a QTRAP 3200TM (hybrid triple quadrupole/linear ion trap) mass spectrometry system (SCIEX, Foster City, CA). The analytical methods will be developed and optimized for targeted and untargeted analyses of metabolites, such as steroidal hormones (dehydroepiandrosterone, androstenedione, testosterone, dihydrotestosterone, estrone, and estradiol), fatty acids (oleic acid; cis, elaidic acid; trans, palmitic acid; saturated), and endogenous small metabolites closely related to energy metabolism and lipid/steroid biosynthesis. Statistical techniques will be used to investigate the particular metabolic changes and entire network of the metabolic pathway profile.

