### Statistical methods

2.8

Data will be displayed as means ± standard deviations for continuous data or n (%) for categorical data. Statistical analyses will be conducted with a 95% confidence interval using the SPSS 21.0 (IBM SPSS Statistics, New York, NY). An independent *t* test will be performed for the comparison of specific biomarkers associated with the pathogenesis of acne by analyzing metabolomics/molecular biomarkers and skin biophysical parameters between the healthy subjects and participants with acne vulgaris. One-way analysis of variance will be performed for the comparison of the differences in these biomarkers among 3 groups (mild, Gr 1-2; moderate, Gr 3-4; severe, Gr 5-6), which we will classify in accordance with the severity of acne using the KAGS. The correlation between the biomarkers and various factors, such as acne symptoms, dietary habit, stress level, sleep pattern, and menstrual pattern, will be examined using the Pearson correlation test. The mean value of a variable will be used in place of the missing data value for that same variable.

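### Sex steroids are compared by an unadjusted t test pooling men and women, while regular menstrual cycles are required of control women only

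*Protocol article*

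**What the plan says.** - **Controls (2.3.1.2).** Women must have had a "regular menstrual cycle during the last 3 months".
- **Acne group (2.3.1.1).** The list has four items: age, body mass index, acne grade and voluntary participation. The grade item sets the severity quotas, for example "20 individuals with KAGS Gr 3 or 4; and 20 individuals with over KAGS Gr 5". No item concerns the menstrual cycle.
- **Shared exclusions (2.3.1.3).** These cover "Use of oral steroids, oral contraceptives, oral vitamin A derivatives, antibiotics, or herbal medicines" in the last 4 weeks, and pregnancy or lactation. Irregular cycles and cycle phase are not mentioned.
- **Targets (2.5.4).** The named serum steroids are dehydroepiandrosterone, "androstenedione, testosterone, dihydrotestosterone, estrone, and estradiol".
- **Data collected (2.5.1).** The questionnaire covers "menstrual pattern and history" and lists polycystic ovary syndrome among the comorbidities to be recorded. Cycle day at the blood draw is not named.
- **Analysis (2.8).** For acne against healthy, an independent t "test will be performed for the comparison of specific biomarkers associated with the pathogenesis of acne". No covariate and no split by sex is stated. Menstrual pattern appears only as one of the factors in a separate Pearson correlation.
- **Numbers (2.7).** 40 healthy participants (20 men, 20 women) and 60 with acne (30 men, 30 women).

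**The concern.** Half of each group is female, and several named targets differ between the sexes or change over the cycle. The plan standardises fasting, alcohol and medication before the draw. It also treats cycle regularity as important enough to be an entry criterion, but for one group only. The stated test then ignores sex and cycle.

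Two consequences follow. Sex and phase variation inflate the error variance of the steroid comparisons. In addition, controls are selected on a reproductive characteristic on which patients are not, so an estradiol or estrone difference in women may partly describe how the controls were chosen. The study aims at diagnostic biomarkers, and a result of that kind could be carried into later work as an acne marker. The separate correlation with menstrual pattern does not adjust the group comparison.

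**Working it through.** **The plan's own figures.** 20 + 20 = 40 controls, 30 + 30 = 60 patients, and three severity strata of 20 make 60. These agree. The plan gives no effect size, SD or power, so no power figure can be reproduced.

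**Inputs.** From 2.7: 20 control women and 30 women with acne. From 2.8: 95% confidence, taken as two-sided alpha 0.05. Assumptions: 80% power, and every quantity below describing the size of sex or phase effects.

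**1. Detectable difference in women, phase ignored or absent.** The normal approximation is (1.960 + 0.842) × √(1/20 + 1/30) = 2.802 × 0.2887 = 0.81 SD. The noncentral t gives 0.825, that is 0.83 SD.

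**2. Loss of precision from phase.** Let r be phase variance divided by phase-free variance. If phase is ignored, the SD grows by √(1 + r), so the detectable difference is 0.825 × √(1 + r) phase-free SD. The last column is the power left for a difference of 0.825 phase-free SD.

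| r (assumed) | Detectable difference | Power |
|---|---|---|
| 0 | 0.83 | 80% |
| 0.5 | 1.01 | 63% |
| 1 | 1.17 | 51% |
| 2 | 1.43 | 37% |

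**3. Pooling the sexes.** Both groups are planned half and half by sex, so pooling adds variance, not bias, if the quotas are met. With a sex gap of g within-sex SD, the pooled variance is 1 + g²/4. For 40 against 60 the normal approximation is 2.802 × √(1/40 + 1/60) = 0.57 SD, to be multiplied by √(1 + g²/4). At g = 2 this is 0.57 × 1.41 = 0.81, the same as for one sex alone at 20 against 30. This assumes the same acne effect and within-sex SD in men and women.

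**4. When bias arises.** With two phases, the spurious difference is the phase gap times the difference between groups in the share of women in the higher phase. If the shares are equal it is zero. In 20,000 simulated trials with no acne effect, half of each group in the higher phase and gaps of 1, 2 and 3 SD, the women-only t test rejected in 4.9% to 5.0%. Equal mix therefore costs precision only. The documents give neither the gap nor the shares.

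**5. Why an *irregular* phase category does not help.** The control criterion leaves no irregular control women. In a model with group and phase, an *irregular* category would hold women with acne only, and its own coefficient would absorb their mean. They would add nothing to the group coefficient. A numerical check with 20 controls and 30 women with acne, 9 of them irregular, gave the same group estimate as the model restricted to regular cycles.

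**6. Cost of restriction.** If 9 of 30 women with acne are irregular (assumption), 20 against 21 remain. The noncentral t then gives a detectable difference of 0.90 SD instead of 0.83 SD.

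**The case against.** The asymmetry may be deliberate: patients as they present, compared with strictly healthy controls. Controls alone are also screened for digestive symptoms and abdominal tension. Polycystic ovary syndrome is recorded rather than excluded, and menstrual pattern is itself an object of study. Conditioning on regularity could remove hormone differences that belong to the disease. This stands, and it is why the as-presented contrast should be kept beside the restricted one.

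A reader might infer that the steroid contrasts are biased, or put a figure on the bias. The documents do not support that. Both groups are recruited at the same time (2.2), no text ties visits to the cycle, and among regularly cycling women there is no stated reason for the phase mix to differ. Imbalance would have to come mainly through irregular cycles in the acne group, whose number is unknown. Any bias figure would be one assumed quantity times another.

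It can also be said that the article condenses a fuller protocol, that the schedule table is not shown, and that the menstrual questions may already include last period and cycle length. A draw-timing rule could exist. It would reduce phase noise, but it would not change the eligibility asymmetry or the stated test.

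Finally, 2.7 describes an exploratory study not sized by power, and the steroids are a few analytes in a large panel. That limits the weight of the point. But 2.8 does fix a test, and for these analytes it is a poor one.

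**Conclusion.** The point holds as a cheap improvement to a stated method. The text fixes three things: a cycle criterion on one side only, sex steroids among the targets, and an unadjusted comparison with no split by sex. Sex and phase variation therefore enter the error term, and a steroid difference in women cannot be separated from the selection of controls.

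The size is not determinable from the documents. The rise in detectable difference shown above rests on assumed variance ratios and on 20 against 30 women, a comparison that arises only once the sexes are analysed separately. It is also the most that adjustment could recover, because recalled cycle dates remove only part of the phase variance. Bias is possible but not shown; it requires a different phase or anovulation mix in the two groups.

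**What to change.** 1. If they are not already among the menstrual questions in 2.5.1, record the first day of the last period and the usual cycle length, and derive cycle phase at the blood draw.
2. In 2.8, analyse the steroid hormones separately by sex.
3. In women, report two contrasts: (a) all women with acne against controls, unadjusted for phase, labelled as the as-presented contrast; (b) women with regular cycles in both groups, in a linear model with group and cycle phase.
4. Do not present a model with *irregular* as a phase category as using all women, since its group estimate is that of (b).

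**Cost.** Up to two questionnaire items and a few sentences in 2.8, with no change to visit scheduling. Contrast (b) uses 1 to 3 degrees of freedom and loses the irregular women with acne. Analysis by sex replaces 40 against 60 with 20 against 30; on the assumptions in step 3 of the working, it detects smaller differences than the pooled test only for hormones whose sex gap exceeds about 2 within-sex SD. For the others, its gain is that the result in each sex can be interpreted.

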##### Exclusion criteria

2.3.1.3

Participants who will meet any of the following will be excluded:1.Use of oral steroids, oral contraceptives, oral vitamin A derivatives, antibiotics, or herbal medicines that may affect the test results during the last 4 weeks.2.No fasting for more than 8 hours after 9:00 pm on the day before the visit.3.Alcohol drinking within the last week.4.Smoking.5.Pregnancy or lactation.6.Judgment that physical or mental testing is not appropriate for the clinical trial.7.Participation in other clinical trials that may affect this trial.

### Recruitment

2.4

Through advertisements, 60 patients with acne vulgaris and 40 healthy participants will be recruited at Kyung Hee University Korean Medicine Hospital. Advertisements will be posted on the notice boards of the hospital and local community centers. Consent will be obtained by the investigators with the principle of informed consent, which confirms the participants’ voluntarism. The participants will sign the consent form that would include the information on the use of their human-derived biomaterials, that is, blood sample.

### Outcome measures

2.5

According to the schedule depicted on Table 1, we will use a series of outcome measures. There will be no difference in the outcomes measured between the patients with acne vulgaris and healthy subjects, except for the pattern identification related to acne symptoms. Facial photoshoot will be performed only on the participants with acne vulgaris. Five milliliters of whole blood will be collected in both patients with acne and healthy participants. The sera will be obtained from the whole blood via centrifugation 30 to 60 min after blood sampling.

**Table 1 T1:**
[figure not shown]
Study schedule for data collection and outcome measures.

#### Questionnaire

2.5.1

The participants will complete a questionnaire that would include general sociodemographic information (e.g., age and sex), personal habits (e.g., smoking, alcohol consumption, sleep pattern, and dietary habits),^[4,13]^ anthropometric measurements (e.g., height, weight, and BMI), pregnancy, menstrual pattern and history, use of oral contraceptives, history of adolescence acne, history of acne in relatives, relevant comorbidities (e.g., polycystic ovary syndrome, hirsutism, type II diabetes, and thyroid disease), acne pattern identification,^[14]^ and stress level during the last month, which will be self-assessed in accordance with the stress response inventory.^[15]^

#### Acne severity using the KAGS

2.5.2

Acne severity is defined in accordance with the KAGS shown in Table 2^[16]^ using photographs limited to the face to help with the assessments. A Lumix DMC-LX2 digital camera (Panasonic, Osaka, Japan) will be used to photograph the front and both sides of each patient's face, so that the inflammatory and noninflammatory lesions can be counted independently.

**Table 2 T2:**
[figure not shown]
Korean acne grading system.

#### Skin biophysical measurements

2.5.3

All biophysical measurements will be performed under strictly controlled conditions with a room temperature of 22 ± 2°C and a relative humidity of 50 ± 10% and after the resting period of ∼30 minutes. The participants will be instructed to follow certain guidelines before testing, that is, not to use cosmetics and not to wash the skin areas to be studied for ∼5 hours before the measurements. The measurements will be performed on the right and left upper cheeks, in the middle of both the eyebrows, and in the middle of the chin. All skin biophysical measurements will be conducted in accordance with the current guidelines.^[17]^ The skin biophysical parameters will be measured before and after the treatment using Sebumeter SM815, Skin-Thermometer ST500, and Reviscometer RVM600.^[18,19]^ Statistical analysis will be conducted with the average values of triplicate measurements for each parameter.

#### Exploring biomarker with metabolomic profiling

2.5.4

This study will apply MS-based metabolomic profiling studies for the detection and identification of potential metabolic biomarkers for acne in the participants’ serum. The liquid chromatography-mass spectrometry system will consist of a Thermo Scientific Vanquish ultra-high-performance liquid chromatography (UHPLC) system (Thermo Fisher Scientific, Sunnyvale, CA) with a triple ToF 5600+ mass spectrometer system (Triple ToF MS) (SCIEX, Foster City, CA) for untargeted metabolite analysis. The UHPLC system with a QTRAP 3200TM (hybrid triple quadrupole/linear ion trap) mass spectrometry system (SCIEX, Foster City, CA). The analytical methods will be developed and optimized for targeted and untargeted analyses of metabolites, such as steroidal hormones (dehydroepiandrosterone, androstenedione, testosterone, dihydrotestosterone, estrone, and estradiol), fatty acids (oleic acid; cis, elaidic acid; trans, palmitic acid; saturated), and endogenous small metabolites closely related to energy metabolism and lipid/steroid biosynthesis. Statistical techniques will be used to investigate the particular metabolic changes and entire network of the metabolic pathway profile.

#### Exploring biomarker with biological profiling

2.5.5

The whole blood, which will be collected in serum tubes, will be allowed to clot by leaving it at room temperature for 30 minutes. The clot will be removed by centrifuging at 3000 rpm for 10 minutes. All the serum samples will be stored at –70°C until further analysis. The concentrations of the cytokines (interleukin [IL-1α], IL-1β, IL-12β, IL-15, IL-6, and tumor necrosis factor-α) and chemokines (monocyte chemoattractant protein-1 and IL-8) in the serum will be determined using a bead-based multiplex assay for luminex platform (R&D Systems, Minneapolis, MN) according to the manufacturer's instructions and measured using a Luminex 200 system (Luminex Corporation, Austin, TX). Each serum sample will be run in duplicates and averaged to calculate the concentrations. The Enzyme-Linked Immunosorbent Assay kits that will be used to analyze the serum calcium, zinc, and ROS will be purchased from Abcamb (Cambridge, UK). Each product will be used following the instructions provided by the manufacturer. The absorbance will be measured at 450 nm using the microplate reader (Versa Max) and analyzed using the SoftMax pro software (Molecular Devices).

#### Standard operating procedures for quality assurance

2.5.6

We have established detailed standard operating procedures for this clinical trial, educated all practitioners, and set qualification standards to make sure the participants in accordance with the trial protocol. Practitioners and medical equipment managers attended a 2-day training workshop on the trial procedures and were educated on the methods of obtaining the photograph of the patients’ face and of using the KAGS, Sebumeter SM815, Skin-Thermometer ST500, and Reviscometer RVM600. A written protocol and standardized recording documents will be provided.

### Data collection, management, and quality control

2.6

To maintain the quality of this trial, and data management including data collection, validation, and completion will be conducted by the Kyung Hee Korean Medicine-Clinical Trial Center (K-CTC) in Seoul, Korea. To ensure that outcome assessments are of a high standard in accordance with the trial protocol, the investigator and the assistants will attend a 6-hour training workshop prior to the initiation of the trial. The investigator and the assistants will also be provided with a written protocol and standard operating procedure documents. All the data will be checked regularly by clinical trial coordinators from K-CTC.

### Sample size

2.7

The current study is a preliminary cross-sectional trial with the aims of discovering novel specific biomarkers in acne by investigating metabolomics/molecular biomarkers between healthy individuals and patients with acne, comparing the differences in these biomarkers according to the severity of acne, and exploring the correlation between the biomarkers and acne symptoms. In other words, this study is, to the best of our knowledge, the first of its kind and not intended to validate affirmatively the effects of certain interventions on acne, but rather to compare the biomarkers of patients with acne with those of healthy individuals. If the aims of the pilot study do not include any hypothesis tests, the power level of a test procedure is not a valid consideration for sample size.^[20]^ Moreover, in the metabolomics study design, a sample size of 3 to 5 per group may give useful preliminary data that can be used to design more elaborate and/or targeted metabolomics studies and the number of sample size for a metabolomics experiment depends on the biological variability associated with the system being studied compared with the analytical variability of the analytical system.^[21]^ Therefore, in this exploratory study, the number of patients to be included will be set to 40 healthy subjects (20 men and 20 women) and 60 patients with acne (30 men and 30 women) which enables the assessment of the difference in metabolomics/molecular biomarkers between healthy individuals and patients with acne including a respective 95% confidence interval, with sufficient precision according to the size of the metabolite kit with expert opinions in metabolomics, molecular biology, dermatology, and statistics.

### Statistical methods

2.8

Data will be displayed as means ± standard deviations for continuous data or n (%) for categorical data. Statistical analyses will be conducted with a 95% confidence interval using the SPSS 21.0 (IBM SPSS Statistics, New York, NY). An independent *t* test will be performed for the comparison of specific biomarkers associated with the pathogenesis of acne by analyzing metabolomics/molecular biomarkers and skin biophysical parameters between the healthy subjects and participants with acne vulgaris. One-way analysis of variance will be performed for the comparison of the differences in these biomarkers among 3 groups (mild, Gr 1-2; moderate, Gr 3-4; severe, Gr 5-6), which we will classify in accordance with the severity of acne using the KAGS. The correlation between the biomarkers and various factors, such as acne symptoms, dietary habit, stress level, sleep pattern, and menstrual pattern, will be examined using the Pearson correlation test. The mean value of a variable will be used in place of the missing data value for that same variable.

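### Sex is balanced by quota in both groups but left out of every planned test, so precision is lost for any marker with a large sex difference

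*Protocol article*

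**What the plan says.** The Sample size section of the protocol article sets "40 healthy subjects (20 men and 20 women) and 60 patients with acne (30 men and 30 women"), so each group is exactly 50% men. The section on metabolomic profiling names, among the target metabolites, "steroidal hormones (dehydroepiandrosterone, androstenedione, testosterone, dihydrotestosterone, estrone, and estradiol").

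The Statistical methods section names its tests. For healthy against acne, an independent t "test will be performed for the comparison of specific biomarkers associated with the pathogenesis of acne", applied "by analyzing metabolomics/molecular biomarkers and skin biophysical parameters between the healthy subjects and participants with acne vulgaris". For severity, "One-way analysis of variance will be performed for the comparison of the differences in these biomarkers among 3 groups". For lifestyle and symptom factors, a Pearson correlation. It adds that "Statistical analyses will be conducted with a 95% confidence interval". No sex term, sex stratum or by-sex analysis appears anywhere in the article, although the questionnaire records sex.

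On size, the article argues that where a pilot study tests no hypotheses "the power level of a test procedure is not a valid consideration for sample size". It rests the numbers on estimating the group difference with a 95% interval "with sufficient precision according to the size of the metabolite kit with expert opinions".

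The inclusion criteria ask for 20 patients in each of three severity bands and state no sex quota within a band.

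**The concern.** The design controls a factor that the analysis then ignores. A two-sample t test on pooled sexes estimates its error SD from men and women together, so any male-female gap in a marker counts as noise. With the quotas fixed, that noise does not affect the true uncertainty of the group difference; it only inflates the estimated uncertainty. The reported interval is then wider than it should be, and the real type I error falls below 5%.

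This matters most for markers on which the sexes differ strongly, plausibly some of the six steroid hormones. A discovery study could pass over such a marker. Interval width is also the article's own reason for its sample size.

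The other two analyses carry a different risk. Nothing stated keeps sex balanced across severity bands, or between high and low values of a lifestyle score. There, leaving sex out can produce a false association as well as lose precision.

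**Working it through.** **Inputs.** From the article: 40 healthy (20 men, 20 women), 60 acne (30 men, 30 women), 95% intervals (taken as two-sided 0.05), 20 patients per severity band. Assumed, because the article gives none: a male-female gap of D within-sex SDs, equal SDs in both sexes, and an acne effect of 0.6 within-sex SD that is the same in both sexes. The sample size itself cannot be reproduced, since no effect, SD, power or target width is stated.

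**Precision without a sex gap.** The standard error of the difference is √(1/40 + 1/60) = 0.204 SD. The half-width is 1.984 × 0.204 = 0.405 SD.

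**Precision with a sex gap.** With 50% men in each group, the pooled SD becomes about √(1 + D²/4) within-sex SDs. With the exact degrees of freedom it is √[(98 + 100·D²/4)/98]. At D = 2 this is √(198/98) = 1.42, and the half-width is 0.405 × 1.42 = 0.58.

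**Power.** The quotas keep the true standard error at 0.204, so the planned test rejects roughly when the observed difference exceeds the inflated half-width. At D = 4 that needs 0.913 against a true 0.6: (0.913 − 0.6)/0.204 = 1.53, a probability of about 6%. At D = 2: (0.576 − 0.6)/0.204 = −0.12, about 55%. Simulation with fixed quotas (20,000 runs) agrees:

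| D | Interval too wide by √(1 + D²/4) | Half-width, t test | Power, t test | Power, sex in model | Type I error, t test |
|---|---|---|---|---|---|
| 0.5 | 1.03 | 0.42 | 81% | 83% | 4.6% |
| 1 | 1.12 | 0.45 | 76% | 83% | 2.7% |
| 2 | 1.41 | 0.58 | 55% | 83% | 0.5% |
| 4 | 2.24 | 0.91 | 7% | 83% | about 0% |

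With sex in the model the half-width stays near 0.41 at every D and type I error near 5%. The mean estimated difference is 0.60 for a true 0.60 throughout, so there is no bias. (A standard power formula with the inflated SD would give 26% at D = 4. It treats the inflated SD as the real sampling error, which fixed quotas prevent, so the simulated 7% is the one to use.)

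**Severity comparison.** Suppose men number 6, 10 and 14 across mild, moderate and severe (assumed; it sums to the 30 men planned). The extreme bands then differ in mean by D × (14 − 6)/20 = 0.4D through sex alone. A marker unrelated to severity is called significant in about 11% of simulated runs at D = 1, 22% at D = 2 and just under 40% at D = 4. With 8, 10 and 12 men there is no inflation above 5%.

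**Correlations.** If a marker and a factor differ by sex by A and B within-sex SDs but are unrelated within each sex, pooling 50 men and 50 women gives r = (AB/4)/√[(1 + A²/4)(1 + B²/4)]. For A = 2, B = 0.5: 0.25/√(2 × 1.0625) = 0.17, significant in about 41% of runs. For A = 2, B = 1: 0.5/√(2 × 1.25) = 0.32, significant in about 92%.

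**The case against.** The strongest reply is that the error in the main comparison is on the safe side: the contrast is unbiased and false positives become rarer. The study calls itself exploratory, sets power aside and lists the absence of a power analysis as a limitation. Lost precision on some markers is then a matter of efficiency. That stands, and it settles the grade. It does not remove the point, because the article claims sufficient interval precision and plans three kinds of test.

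A reader might infer that intervals are far too wide and real differences missed across all markers. The documents do not support that. They give no male-female gap for any marker, and the gap decides everything. For cytokines, zinc, calcium, reactive oxygen species and the skin measures, nothing in the article points to a large gap; where the gap is 0.5 SD or less, the interval is about 3% wider or less.

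A reader might also suspect confounding by age. Both groups share the limits of 19 to 35 years, and no imbalance is shown.

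Nor does adding sex as a main effect recover acne effects that run in opposite directions in men and women. With opposite effects of 0.6 SD, the group-plus-sex model has about 4% power. Only an interaction term can show this, and its power for an effect of 0.6 SD in women alone is about 31%.

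Finally, covariates are often left to an analysis plan, which is not shown here. This carries limited weight, because the article names each test and none includes sex.

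**Conclusion.** The point holds conditionally. The planned t test discards precision that the sex quotas make available. The loss is negligible at a sex gap of 0.5 within-sex SDs or less, moderate at 1 (power 83% to 76%) and severe at 2 or more (55% at 2, 7% at 4). These figures assume equal within-sex SDs and a common additive effect of 0.6 SD. With a 4:1 ratio of within-sex SDs, power with sex in the model is about 70%, still far above the t test.

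The healthy-acne mean difference is not biased by sex. Confounding of the severity comparison is a risk only if the bands differ clearly in sex mix. Confounding of a correlation is a risk only where marker and factor both differ by sex.

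This is a free improvement, not a defect that must be repaired before the study can proceed.

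**What to change.** In Statistical methods:

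- **Healthy against acne:** replace the t test by a linear model, biomarker ~ group + sex, and report the adjusted group difference with its 95% interval.
- **Severity:** add sex to the analysis of variance.
- **Correlations:** use partial correlations given sex.
- **Six steroid hormones:** also report results by sex, with an exploratory group-by-sex term and a note that its power is low.
- **Age:** may be added as a collected covariate, but nothing in the documents makes it necessary.

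The cost is wording and, in the main comparison, one of 98 degrees of freedom. Sex is already recorded; no extra data or participants are needed.
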